#### Withdrawal criteria

2.2.3

(1) Withdrawal as decided by the investigator:

① During the study, the participant has certain comorbidities, complications, or pathological changes that make it unsuitable to continue the study.② In the study, the participant has poor compliance, which may affect the evaluation of effectiveness and safety.③ The participant breaks the blindness or exposes the blinded data in an emergency.④ Adverse events and serious adverse events occurred, making a participant unsuitable to continue to receive the study.

(2) Withdrawal from the study.

According to the provisions of the informed consent, participants have the right to withdraw from the study midway, or the participants may not explicitly withdraw from the study, but may no longer receive medication and testing, and lose follow-up (which is also classified as a “withdrawal,” called “drop”). The reasons for withdrawal, such as poor efficacy, intolerance to certain adverse effects, inability to continue the clinical study, economic factors, and failure to explain the reasons for the loss of visits, should be understood as much as possible and recorded.

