### Randomization and allocation concealment

2.3

In this study, a centralized randomization system developed by the research team randomly assigned patients to the acupuncture and sham acupuncture groups in a 1:1 ratio. The module size was set to 4, and 37 patients were randomly assigned to each group. All assignment information was unpredictable and invisible until participant inclusion, and the assignment sequences were directly notified to the acupuncturist by the system to ensure fairness of the assignment sequence hiding and randomization process. After the investigator confirms the qualified cases, a third party submits the application to the central randomization system, which automatically assigns the group information according to the randomization method and sends the group information to the investigator and acupuncturist.

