### Data processing and statistical analysis

2.10

Data analysis was performed by qualified personnel not involved in the study using the Modified Intention-to-treat (mITT) principle. mITT was defined as participants who were randomized, received at least one treatment, and were statistically analyzed using the SPSS (IBM SPSS Statistics, Version 26.0) software. The significance level was set at 5%. Continuous variables that conform to the normal distribution are represented by mean ± standard deviation (x ± s), and non-normal continuous variables are represented by median and quartile [M (P25, P75)]. Categorical variables are expressed as frequency (percentage) using a chi-square or Fisher precision test. For primary and secondary outcomes, an independent sample T-test was used to compare groups if normal distribution and homogeneity of variance were met; otherwise, the Mann–Whitney *U* test was used. Intragroup comparisons were performed using the paired sample T-test. According to missing outcome data, the last observation carried forward (LOCF) method or multiple interpolation was used to fill in the missing values. In addition, sensitivity analyses were performed to clarify the robustness of the results by comparing the conforming protocol analysis set (PPS) analysis with the ITT analysis set. The data obtained by sEMG were analyzed with the main outcome, FMA-UE, using Person/Spearman correlation analysis. Finally, we calculated the BI index to evaluate the success of blinded implementation.

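### The stated robustness check (PPS versus an ITT set that is not the defined mITT set) does not rule out bias from outcome-related withdrawal

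*Protocol article*

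**What the plan says.** The Protocol article, section 2.10, states that data are analysed "using the Modified Intention-to-treat (mITT) principle" and gives the definition: "mITT was defined as participants who were randomized, received at least one treatment". For missing outcomes it says that "the last observation carried forward (LOCF) method or multiple interpolation was used to fill in the missing values"; I read the second option as multiple imputation. The sensitivity analysis it states is "comparing the conforming protocol analysis set (PPS) analysis with the ITT analysis set". It defines neither the PPS nor the ITT set.

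Section 2.2.3 lists why patients may leave. For patients' own withdrawal it names "The reasons for withdrawal, such as poor efficacy, intolerance to certain adverse effects", among others, and asks that reasons be recorded. For withdrawal decided by the investigator it includes "the participant has poor compliance, which may affect the evaluation of effectiveness and safety" and "Adverse events and serious adverse events occurred, making a participant unsuitable to continue to receive the study". Section 2.5 allows for 20% dropout when it arrives at 37 patients per arm.

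**The concern.** There are two linked problems. First, one paragraph defines one analysis set and tests robustness on another. Read literally, the comparison is between two sets neither of which is the main analysis; read loosely, ITT is a slip for mITT. The text does not settle which.

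Second, several of the foreseen reasons for leaving are related to how the patient is doing, and may differ between real and sham needling. The patients whose outcome is in doubt are left out of one side of the comparison and carry filled-in values on the other. If the two results agree, a reader will take the FMA-UE conclusion as robust to withdrawal, although the comparison has not examined that question.

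**Working it through.** **Expected number of leavers.** Inputs from section 2.5: difference 11.5, SD 10.4, margin 4.6, α = 0.05, power 0.8, dropout 20%. With difference 11.5 − 4.6 = 6.9 and a one-sided 0.05 test, the calculation gives 29 per arm, 58 in total, as stated. Then 29 / 0.8 = 36.25, rounded up to 37 per arm, 74 in total. The plan's figures reproduce. The expected loss is 0.20 × 37 = 7.4, about 7 per arm.

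**What each analysis gets wrong.** In one arm let f be the share who leave, S the mean of those who stay, L the mean the leavers would have had, and F the mean of the values filled in for them. The true arm mean is (1 − f)S + fL.
- PPS, taken as stayers only, uses S. Error = f(S − L).
- The filled-in full set uses (1 − f)S + fF. Error = f(F − L).
- Gap between the two = f(S − F).

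The gap does not contain L. It shows how far the filled-in values lie from the stayers, not how the leavers would have scored. A large gap would show that the handling of leavers matters; a small gap says nothing about L. Multiple imputation that treats leavers as resembling comparable stayers brings F close to S, so it shrinks the gap whatever L is.

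**Size.** Bias in an arm mean = dropout share × shortfall. The shortfalls are assumptions; the documents give none.
- 5 points: 0.20 × 5 = 1.0
- 11.5 points (the size of the pilot difference, used only as an upper scenario): 0.20 × 11.5 = 2.3, and 2.3 / 4.6 = 0.5 of the margin
- For 5.2 points, the bias runs from 0.10 × 5.2 = 0.52 to 0.30 × 5.2 = 1.56 as the missing share goes from 10% to 30%

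A shortfall confined to the MA arm overstates the acupuncture effect; one confined to the SA arm understates it; equal shortfalls cancel.

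**Illustrative simulation.** Assumptions, none of them trial figures except the SD and the numbers per arm: no true effect, mean gain 8, SD 10.4, 7 of 37 lost per arm, leaving correlated 0.7 with poor gain where it is selective, last value equal to baseline, 5,000 runs.

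| Who leaves | PPS-type bias | LOCF full-set bias | Two-sided rejection at 5% (PPS, LOCF) |
|---|---|---|---|
| Poor responders in MA, random in SA | +2.46 | +2.00 | 16.6%, 13.1% |
| Poor responders in SA, random in MA | −2.38 | −1.93 | 16.7%, 13.0% |
| Poor responders in both | +0.05 | +0.04 | 6.7%, 4.3% |

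In the first two rows the analyses differ by 2.46 − 2.00 = 0.46 and 2.38 − 1.93 = 0.45 points, while both are wrong by about 2 in the same direction. Most of the LOCF bias in the first row comes from giving zero gain to SA patients who left at random: 7/37 × 8 = 1.5. Only about 2.0 − 1.5 = 0.5 comes from MA leavers scoring below their carried-forward values. The simulation therefore shows that two analyses can agree and both be wrong. It does not confirm the 2.3-point scenario.

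**The case against.** The strongest reply is that a journal article condenses. Section 2.1 says that protocol and analysis plan details are available under the registration number, and set definitions or further sensitivity analyses may be there. Comparing PPS with ITT is a routine look at adherence, and section 2.10 does not label it a check for withdrawals. This stands in part: a reader might infer that the trial has no other sensitivity analysis, and the article cannot show that. What remains is what the article does fix, namely two set names that do not match and a PPS comparison given the task of showing robustness.

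The naming conflict may also be loose wording. If ITT means mITT, the conflict is only a label. If it means all randomized patients, part of the remedy is already planned, as a side analysis. Either way the passage needs correcting, and in neither case is the assumption about leavers varied.

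A reader might infer that PPS versus ITT cannot detect such bias at all. That goes too far: a large gap could raise an alarm. The article also does not define PPS, so its omission of leavers rests on the usual meaning of the term.

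A reader might infer that the plan overstates acupuncture by 2.3 points. The documents do not support that. The 11.5 is a between-group pilot difference, borrowed here as a one-arm shortfall, and the direction depends on which arm loses its poor responders. For scale, if the trial reproduced the pilot difference, a one-arm shortfall of (11.5 − 4.6) / 0.20 = 34.5 points would be needed to bring the point estimate down to the margin. A conclusion based on a test or confidence limit would change sooner.

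Finally, section 2.3 says the system "sends the group information to the investigator and acupuncturist", so a reader might infer that exclusion of never-treated patients from mITT is driven by arm. It could be, but nothing indicates how many such patients there will be. Participants are inpatients, so the number is probably small.

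**Conclusion.** The point holds in limited form and should be acted on. Section 2.10 names an analysis set and a robustness comparison that do not match. Agreement between PPS and a filled-in full set does not rule out bias from the outcome-related withdrawal that section 2.2.3 foresees. At 20% dropout and assumed shortfalls of 5 to 11.5 points, the bias in an arm mean is 1.0 to 2.3 points. It lies towards or against acupuncture according to which arm loses poor responders, and is about zero if both arms lose them alike. This rests on the usual meaning of PPS, on the planned dropout rate occurring, and on shortfalls that are scenarios and not estimates.

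**What to change.** In section 2.10, make all randomized patients, analysed in the arm assigned, the primary set, and use one name for it throughout. State what PPS excludes and keep it as supportive only.

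Add, as the sensitivity analysis for missing FMA-UE, a multiple imputation in which a penalty is subtracted from the imputed scores of patients who left. Use the recorded reasons to decide to whom it applies (poor efficacy, adverse effects). Vary the penalty separately in MA and SA, from zero upward, and report the values at which the conclusion changes so that readers can judge whether they are plausible.

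The cost is revised wording and a few hours of programming. The sample size does not change and no new data are needed, since withdrawal reasons are already to be recorded. The one downside is that including never-treated patients may slightly dilute the estimate.

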**Conclusion:**

This study assesses the effectiveness and safety of acupuncture for post-stroke upper limb impairment in multiple aspects and elucidates the underlying neuromuscular effect mechanism of acupuncture to provide clinical evidence.

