### Sample size

2.5

The sample size calculation for this study was based on the primary outcome measure, the FMA-UE score. According to preliminary pilot results, the mean difference (MD) in FMA-UE scores between the acupuncture and control group after treatment was 11.5, with a standard deviation (SD) of 10.4. Meanwhile, the minimal clinically important difference (MCID) for the Chinese version of the FMA-UE is 4.6. This study was a superiority design, using PASS 15.0 software for sample size estimation. An independent samples t-test was employed, with a significance level set at *α* = 0.05 and power *β* = 0.8. It is estimated that the acupuncture group must reach the MCID value compared to the sham acupuncture group to be clinically meaningful. Therefore, the superiority margin is set equal to the MCID value of 4.6. The minimum sample size calculated is 58 cases. Considering a 20% dropout rate, the final sample size was determined to be 74 cases (37 cases each in the MA and SA groups).

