#### Other outcomes

2.7.3

sEMG is a technique for recording the bioelectrical signals of the neuromuscular system during muscle activity (13), which can quantify muscle functional status. It was recorded using a 10-channel multi-lead 060525001 Myotrac3 surface electromyograph (THOUGHT, Canada). The evoked potentials of the core upper limb muscle groups (including pectoralis major, deltoid, biceps brachii, triceps brachii, brachioradialis, etc.) defined by neuroanatomy experts were collected. The specific indicators include the root-mean-square value (RMS) and integrated electromyography value (iEMG) of the time-domain indicators, which quantify the overall muscle activation strength from the perspectives of transient intensity and cumulative loading, respectively. Frequency domain indicators include the median frequency (MF), defined as the frequency point corresponding to 50% of the energy accumulation in the spectrum, to infer muscle fiber conduction velocity (MFCV), which is used to assess muscle fatigue (28). Before collection, evaluators need to undergo standardized training to regulate the movement patterns of the core muscle groups; then the evaluators guide the patients in exercise to practice and master the standardized movement methods; secondly, before collection, the signal acquisition parameters of the instrument need to be pre-tested to ensure parameter stability. The specific operation is as follows: Inform the patient before the test to perform relevant actions according to sEMG. The patient is in a sitting position before applying the electrode sheet, local hair removal is carried out on the site where the electrode sheet is to be applied, the skin surface is polished with a special sanding pad, and then wiped with an ethanol cotton ball to remove the skin cuticle, reduce the contact resistance between the electrode and the detection surface, and protect the electrode to avoid movement and avoid errors as much as possible. After completing the electrode affixing, the electromyographic signal becomes stable, and detection begins. According to the machine’s instructions, the doctor and patient cooperate to complete the corresponding active and passive movements. Each movement lasts for 15 s, followed by a 5-s rest. Each movement is repeated 3 times as one set, with a 1-min rest after each set. The middle 10 s of the electromyographic signal for each movement is used for analysis.

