In addition, the efficacy evaluation of acupuncture treatment for post-stroke upper limb dysfunction currently mostly uses scales. Although the sensitivity and specificity of subjective assessment tools have improved compared to before (35), they still cannot avoid interference from subjective factors of evaluators and patients, which may ultimately lead to bias in acupuncture efficacy. As a tool reflecting effect mechanisms, sEMG has been widely used in recent years for the objective assessment of post-stroke limb function. By recording muscle activity information during movement or rest (such as contraction timing, location, and intensity) and performing time-frequency analysis to quantify peripheral bioelectrical parameters like muscle co-contraction rate and motor unit recruitment timing, it visualizes muscle electrical activity and evaluates muscle activation patterns (36). However, there are currently few RCT studies combined with sEMG. Therefore, this study innovatively integrates sEMG and related scales, using both subjective and objective indicators to conduct a multidimensional assessment of acupuncture’s improvement on post-stroke upper limb function. The aim is to overcome the limitations of single efficacy evaluation and weak mechanism explanation, achieving dynamic and visualized analysis of the acupuncture effect mechanism. In addition, this study also conducts correlation analysis between the scales and sEMG indicators, intending to establish a comprehensive evaluation system of the “functional recovery-muscle synergy” full chain, further exploring the neuromuscular driving mechanism.

However, the clinical application of sEMG still faces a major challenge: its data collection is easily affected by various confounding factors such as the environment, leading to inaccurate evaluation of sEMG efficacy. Therefore, to control the quality of data collection, we specify the muscle movement paradigm before collection, uniformly treat the subject’s skin tissue, use standardized electrodes and instruments during collection, isolate the patient from environmental noise, and improve the accuracy of results by controlling the influence of these related operational factors.

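### If the arms are pooled, the unadjusted sEMG–FMA-UE correlation can reflect the treatment effect alone; adjust it for arm and report it as an association

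*Protocol article*

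**What the plan says.** Section 2.10 names the method in one sentence: "The data obtained by sEMG were analyzed with the main outcome, FMA-UE, using Person/Spearman correlation analysis". It does not say whether the two arms are analysed together, whether levels or changes are used, or at which visit. The general significance level in that section is 5%.

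The Discussion gives the purpose. It says that "this study also conducts correlation analysis between the scales and sEMG indicators", with the intention of "further exploring the neuromuscular driving mechanism". The abstract's conclusion goes further and says that the study "elucidates the underlying neuromuscular effect mechanism of acupuncture to provide clinical evidence".

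Section 2.7.3 lists the sEMG measures: the "root-mean-square value (RMS) and integrated electromyography value (iEMG) of the time-domain indicators", plus the median frequency, on several upper limb muscles. Table 1 schedules both sEMG and the FMA at baseline and at week 4.

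**The concern.** A plain Pearson or Spearman coefficient has no place for treatment arm. In a randomised two-arm trial, arm is a possible common cause of both variables. If acupuncture raises FMA-UE and also shifts an sEMG index, the acupuncture patients lie high on both and the sham patients low on both. The pooled scatter then slopes even if, inside each arm, a patient's sEMG says nothing about that patient's FMA-UE.

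The artefact grows with the two treatment effects. It is therefore largest when the trial succeeds on both measures, which is also when a statement about mechanism is most likely to be made. A pooled, unadjusted correlation cannot distinguish a link between muscle activation and function from two parallel effects of the same treatment.

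**Working it through.** **Inputs from the protocol article**
- Section 2.5: the FMA-UE difference "after treatment was 11.5, with a standard deviation (SD) of 10.4"; superiority margin 4.6; 58 patients before dropout; 74 randomised (37 per arm).
- Section 2.5 also states the error rates: "with a significance level set at *α* = 0.05 and power *β* = 0.8".

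**Assumptions**
- The document gives no sEMG effect, so a range of 0 to 2.0 SD is used.
- Data are normal with equal variances.
- The within-arm correlation between sEMG and FMA-UE is zero, so every significant result is a false positive for a within-arm link.
- The test is two-sided at 5%.

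**Step 1: reproduce the plan's own figure.** No figure is given for the correlation, so the check is on the sample size that supplies the inputs. With a net difference of 11.5 − 4.6 = 6.9 and one-sided 0.05, n per arm = 2 × (1.645 + 0.842)² × (10.4/6.9)² = 28.1. This rounds up to 29, or 58 in total, and the exact t calculation also gives 58. For 20% dropout, 29/0.8 = 36.25, which rounds up to 37 per arm, or 74. The stated figures reproduce. (Two-sided, the total before dropout would be 72, or 74 by the t calculation.)

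**Step 2: expected pooled correlation.** Let d1 and d2 be the standardised effects on FMA-UE and sEMG. With 1:1 allocation and no within-arm relation, the pooled covariance is d1·d2/4 and the pooled variances are 1 + d1²/4 and 1 + d2²/4. Hence

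r = (d1·d2/4) / √[(1 + d1²/4)(1 + d2²/4)].

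Here d1 = 11.5/10.4 = 1.106 and d1²/4 = 0.306. For d2 = 0.5, r = 0.138 / √(1.306 × 1.0625) = 0.117. For d2 = 1.106, r = 0.306/1.306 = 0.234.

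**Step 3: how often this is significant.** The critical |r| is 0.229 at N = 74 and 0.259 at N = 58. Rates are from 20,000 simulated trials per scenario, for the pooled Pearson test.

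| sEMG effect (SD) | Expected r, FMA-UE effect 11.5 | N = 74 | N = 58 | N = 74, FMA-UE effect 4.6 | N = 58, FMA-UE effect 4.6 |
|---|---|---|---|---|---|
| 0.2 | 0.048 | 7.0% | 6.5% | 5.5% | 5.2% |
| 0.5 | 0.117 | 17.0% | 14.4% | 7.3% | 6.9% |
| 0.8 | 0.180 | 33.5% | 27.1% | 10.1% | 9.0% |
| 1.11 | 0.234 | 53.5% | 44.0% | 14.3% | 12.0% |
| 1.5 | 0.290 | 73.8% | 63.4% | 19.9% | 16.8% |
| 2.0 | 0.342 | 88.1% | 79.6% | 26.1% | 21.3% |

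The 4.6-point columns use d1 = 4.6/10.4 = 0.44. Spearman gives nearly the same rates. As a plausibility check, at an sEMG effect of 1.11 SD the expected r of 0.234 is just above the critical 0.229, so a rate near one half is what one would expect.

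**Step 4: the alternatives.** A partial correlation adjusted for arm, or a correlation within the acupuncture arm only, rejects in 4.6% to 5.3% of trials in every scenario.

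**The case against.** The strongest objection is that the defect is read into silence. The document does not say that the arms are pooled, and a within-arm correlation has no such artefact. Stratification and the choice of change scores are details that an analysis plan may settle, and section 2.1 says that its details are available under the registration number. This stands in part: the point is conditional on pooling. But a simple correlation with no arm term is what the text names, pooling is its natural reading, and pooling is invalid for the purpose the Discussion gives.

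Several stronger readings are tempting but unsupported.
- **A reader might infer that the correlation is bound to be significant whenever acupuncture moves both measures.** It is not. At N = 74 with the pilot effect, significance is close to a coin toss when the sEMG effect equals the FMA-UE effect, and near nominal for small sEMG effects. Reaching 80% needs an sEMG effect of about 1.8 SD.
- **A reader might infer that nothing else addresses the mechanism aim.** Section 2.7 also plans a before-and-after comparison of the sEMG indices, and section 2.10 includes within-group paired tests.
- **A reader might multiply five named muscles by three indices and quote a family-wise error rate for 15 independent tests.** RMS and iEMG are both amplitude measures from the same signal, so independence is implausible and the figure would be overstated.
- **A reader might infer that a causal or mediation test is claimed.** None is. The Introduction and the Discussion speak of exploring, and sEMG is listed among the other outcomes. Only the abstract's conclusion uses stronger language.

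It is also fair to say that the pilot figures are described as scores after treatment. Treating 1.1 SD as the effect on change scores is therefore an assumption.

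**Conclusion.** The concern holds in a limited form. If the arms are pooled without adjustment, the false-positive rate for a link within arms rises above 5% by an amount that depends on both treatment effects. With the pilot FMA-UE effect and assumed sEMG effects of 0.2 to 1.1 SD, it is about 7% to 54% at 74 patients and 7% to 44% at 58. It is much smaller if the FMA-UE effect is only 4.6 points. These sizes rest on the assumed sEMG effects, normal data, equal variances and zero within-arm correlation. Such a correlation cannot by itself support a mechanism reading. This is a low-cost improvement to an exploratory analysis and does not touch the primary FMA-UE comparison.

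**What to change.** In section 2.10, state that the correlation is between baseline-to-week-4 changes in sEMG and in FMA-UE. Estimate it as a partial correlation adjusted for treatment arm and baseline FMA-UE, or report it separately within each arm. Label it exploratory.

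In the Discussion and in the abstract's conclusion, describe the result as an association and drop the claim to elucidate a mechanism. Adjustment for arm removes the artefact shown here, but it does not turn an association into a mechanism, because an unmeasured common cause may remain.

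If the analysis plan already specifies a within-arm or arm-adjusted analysis, only the wording needs to change.

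The cost is a few lines of code and text. Table 1 already provides both measurements at both visits, so no new data, visits or patients are needed. The downside is fewer nominally significant correlations.
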